### Safety monitoring

Monitoring and measuring safety of the *Dil Mil* intervention is challenging because of the high prevalence of family conflict and DV in this setting. Moreover, because the study plans to recruit young women with previous experience of family conflict and violence, safety monitoring will need to focus on identifying safety-related “events that reasonably might be linked to the intervention [12], p.116.”

Our team has received training to interact with participants in a sensitive and respectful manner and to facilitate disclosure of family conflict and violence. Staff will look for cues of emotional distress and provide emotional support to women who disclose DV. Both DILs and MILs will have the opportunity to meet one-on-one with an experienced counselor during regular clinic hours; appointments during non-clinic hours will be made if necessary. DILs will be encouraged to adhere to their antenatal visit schedule, and maternal and mental health assessments will be conducted to monitor their health during the pregnancy [43]. Antenatal visits will also provide an opportunity for reiteration of information regarding available support services.

On-site counseling and referral support will be made available, with information offered to participants verbally at each study visit, regardless of disclosure of victimization, and at an information counter that study staff have set up at the health centers. We have developed close relationships with support services such as child development agencies, shelters, and legal aid organizations in Bengaluru. Assistance such as escort to a referral care provider or an introductory letter or phone call will be provided to those who want to access these services and need support. Participants will be informed about how to access staff and support services at any point during the study. They will be instructed to contact the project director in the event of any threat to their safety or health due to study participation or other reasons. Referrals will be documented using a Referral Care Form and reviewed on a routine basis to ensure that appropriate care is being provided and to detect any potential study-related risks.

Building on previous intervention trials that have focused on vulnerable populations and included detailed risk appraisals (such as measures of depression and experience of physical harm), we established a safety monitoring system that centered around two types of safety-related events: safety alerts and adverse events. Safety alerts constitute “red flags.” They are events that may pose safety risks to participants, but may not involve participants directly, or if they do, are unlikely to be related to study participation or not considered to be severe. Examples of safety alerts include staff witnessing a family disagreement or conflict that is unrelated to the study, participant report of a minor altercation at home due to study participation, gossip in the community regarding study objectives, or enquiries about the study by family members. Miscarriages among DILs and illness episodes among MILs may be classified as safety alerts if they are determined to be unrelated to study participation. Safety alerts may warrant investigation by the study team to determine relatedness to study activities through discussion with participants and discreet gathering of information in the community (without jeopardizing participant confidentiality). Safety alerts may result in heightened monitoring of interactions with one or more participants, and will be reported to the IRB every six months.

Adverse events are defined as unexpected, unfavorable, and serious events such as serious injury, self-harm, hospitalization, or pregnancy loss that are temporally associated with and likely to be related to study participation. Adverse events will be reported to the IRB within 24 to 48 hours, and may result in substantive changes in the research protocol or other corrective actions in order to protect the safety, welfare, or rights of participants.

Definitions of safety alerts and adverse events were finalized through discussion and consensus among the study team and members of a two-person data and safety monitoring committee (DSMC) established for the study. Staff will be required to report all events without delay to the project director and principal investigators who will be responsible for classifying the event, developing appropriate responses, and reporting to the IRB and DSMC. All events will be recorded on an Incident Occurrence Reporting Form.

A range of resolutions may be pursued in the case of safety alerts and adverse events. These may include offering counseling or referrals, protocol modifications (e.g., change in participant tracking strategy), consultation with community advisors, and/or continued monitoring for recurrence of the event or occurrence among other participants. In our experience, responses to safety alerts need to be determined on a case-by-case basis, in consultation with the participant (when possible) and taking into account their best interests. Thus, our safety monitoring protocol describes guidelines for identifying events and allows for resolutions that are tailor-made to specific situations and cases.

The sensitivity of the issues we propose to address may place research staff in unsafe situations [15,44]. Our experienced staffs are highly trained to negotiate such situations and will have a safety plan to follow in the event of a challenge in the field. Staff safety strategies include working in pairs to recruit and follow-up participants, enlisting the support of community advisors or health center staff when appropriate, having access to a cell phone to contact other staff in case of an emergency, carrying identification badges, having timely and daily debriefs with the project director to discuss any situations of potential concern, and documenting any safety-related challenge/situation for further discussion and action.

### Randomization

Consenting dyads will be randomized as pairs on completion of the baseline assessment. Within each site, dyads will be randomized to ensure treatment balance after every 20 randomizations. The study statistician will employ a pseudo-randomizer software package to determine dyad treatment assignments and provide a series of sealed opaque randomization envelopes to study staff with one envelope per dyad. The participant IDs will be printed on the outside of the envelope, and the assigned study arm will be printed on a card contained in the envelope. A designated staff member at each center will open envelopes in sequential order of participant ID. Post randomization, the project director will ensure that the staff designated to facilitate intervention sessions do not conduct follow-up interviews or vice versa, and interviewers will not have access to information on treatment assignment.

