Safety Monitoring	Defining safety in a context of high prevalence of DV and in a population with prior history of family conflict and violence; Monitoring safety	Classification of safety-related events as “safety alerts” or “adverse events,” with alerts comprising incidents that are highly unlikely to be related to study participation and/or not considered to be severe and adverse events comprising incidents that are unexpected, temporally associated with and likely to be related to study participation and severe; Establishment of rapport with participants and creating a safe environment at the health center by offering information on DV-related resources at every visit, establishing an information desk at study health centers, and providing staff contact information; Presence of on-site counselor
Randomization	Confusion regarding or lack of understanding of randomization	Explanation of randomization in terms of a lottery; Opening of envelope with treatment assignment in front of dyad
Intervention implementation	Stress, discomfort or distress as a result of intervention participation; Loss of confidentiality in group education sessions	Establishing ground rules for group session participation including respect for each other’s views; Inclusion of activities to promote peer support and dialogue, such as co-counseling; Staff trained to handle difficult situations arising during group sessions; Counseling available on site and referral information offered; Child care and food offered; Participants and staff take a pledge of confidentiality regarding personal information shared in the group
Data collection	Stress, discomfort or distress caused by interview questions; Loss of confidentiality	Interviewers trained to conduct interviews with sensitivity and empathy; Use of statements such as, “some women can feel sad or upset by these questions—do remember that you can decide not to answer any question” repeated at strategic points of interview; Counseling available on site and referral information offered; All interviews conducted in closed room at health center; Data identified only through unique numeric identifiers

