### Intervention and control conditions

Dyads will be randomized to the control arm and receive standard care or to the intervention arm and receive standard care plus the *Dil Mil* intervention. Standard care for DILs includes primary care and access to DV-related support services [45,46]. For MILs, we will offer a comprehensive health examination including a gynecological exam and screening for diabetes and hypertension, along with appropriate information, prescriptions, and/or referrals. We will routinely offer DV-related resources, such as information, counseling, and referrals to all participants, DILs and MILs, regardless of study arm.

The intervention, which will be implemented during the second and third trimesters of the DILs’ pregnancy, consists of 2 half-day group sessions with DILs, 5 half-day group sessions with MILs, and one joint half-day session with DILs and MILs. *Dil Mil* is delivered at the health center to small groups consisting of 12 DILs or MILs (i.e., 6 groups of 12 individuals), except for the joint session in which DILs and their MILs participate together.

The curriculum is based on participatory learning and action principles and uses stories, role-play, and discussion to enhance participants’ knowledge, skills, and social support (see [36] for details). Facilitators will encourage participants to critically analyze their relationships and to develop and implement responses appropriate to their families and communities. The group education sessions with MILs will focus on the physical and psyschosocial dimensions of growing older and the impact of life experiences including experience of DV and familial relationships on their current health status. Based on these discussions, MILs will be encouraged to reflect on the health of daughters and DILs. Thus, by beginning and grounding discussions of DV and women’s health in personal experiences and by addressing MILs’ health concerns, we expect to reduce the risks of the intervention to participating DILs.

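### Allocation is balanced at a fixed, published interval of 20 dyads per site in an unmasked trial, so the envelope opener at each centre can know the last assignment of every block in advance

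*Protocol article*

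**What the plan says.** The Randomization section sets the unit and timing: "Consenting dyads will be randomized as pairs on completion of the baseline assessment". It then fixes the balance rule: "Within each site, dyads will be randomized to ensure treatment balance after every 20 randomizations". No variation in the interval is described.

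Concealment is by envelope. The study statistician will "provide a series of sealed opaque randomization envelopes to study staff with one envelope per dyad", and "The participant IDs will be printed on the outside of the envelope". On opening: "A designated staff member at each center will open envelopes in sequential order of participant ID". Table 1 (Randomization row) adds the design response: "Opening of envelope with treatment assignment in front of dyad".

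The same section limits who learns the arm after randomisation. Session facilitators and follow-up interviewers are kept as separate people, and "interviewers will not have access to information on treatment assignment". The arms are standard care with or without group sessions at the health centre (Intervention and control conditions), so dyads and facilitators know the assignment.

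**The concern.** A sealed opaque envelope hides the card inside it. It does not hide the count of cards already opened. If a block is known to hold 10 of each arm, then once one arm has reached 10 the rest of the block is determined. The opener sees every assignment at the centre in order, with the participant ID on each envelope to mark the position.

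Foreknowledge matters only if it can influence which dyad is randomised next. Recruitment and retention describes several staff-run steps: outreach, screening, an approach to the mother-in-law (by staff if the daughter-in-law prefers), and discretion to stop the process when staff sense discomfort or lack of interest. If the person who knows the count takes part in those steps, or talks to someone who does, more cooperative dyads could be favoured when the next place is known to be in the intervention arm.

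The outcomes at stake are largely self-reported attitudes, support and domestic violence, which plausibly track family cooperativeness. The named adjustment variables (age, education and socioeconomic status, in Quantitative assessments and analytic plan) are given as examples, and those three would not capture it.

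**Working it through.** The plan gives no predictability figure to reproduce. Its only number on this point is the interval of 20.

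**Inputs.** Block of 20 within site (Randomization). Three centres (Study setting and design). 144 dyads (Sample size and power analysis). 1:1 allocation, inferred from 6 groups of 12, that is 72 of 144, in the intervention arm (Intervention and control conditions). Assumed: equal sites, so 144/3 = 48 dyads each, and a single permuted block of 20 between balance points.

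**1. Assignments certain in advance, per block.** With m per arm, the expected number is 2m/(m+1). For m = 10: 20/11 = 1.82, and 1.82/20 = 9.1%.

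**2. How far back certainty reaches.** P(last k certain) = 2·C(20−k,10)/C(20,10) for k of 2 or more:
- k = 1: always
- k = 2: 47%
- k = 3: 21%
- k = 4: 9%

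**3. Over the trial.** Each site of 48 has two complete blocks and 8 places of a third. No arm can reach 10 within 8 places, so the partial block adds nothing. Certain per site: 2 × 1.82 = 3.64. Three sites: 10.9 dyads, and 10.9/144 = 7.6%.

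**4. Predictable with at least 80% probability.** Summing over all possible counts within a block gives 2.33 of 20 places. Per site 2 × 2.33 = 4.65, and 4.65/48 = 9.7%.

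**5. Average success of guessing the arm that is behind.** [m + (4^m/C(2m,m) − 1)/2]/(2m) with m = 10 gives 61.7% for a full block. Over 48 dyads, with the partial third block, it is 60.4%. Pure chance is 50%.

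**6. Alternatives.** These were simulated for 48 dyads per site, against a guesser who knows the set of possible lengths and updates on every assignment seen.

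| Scheme | Certain | Predictable at 80% or more | Correct guess |
|---|---|---|---|
| Fixed 20 | 7.6% | 9.7% | 60.4% |
| Lengths drawn freely from 12, 16, 20, 24 | about 0.6% | about 3.5% | about 61% |
| Same lengths, forced to sum to a known 48 | about 4.4% | about 8.6% | about 62.6% |
| Short mixed blocks 4, 6, 8 | about 2.5% | about 23% | about 68% |

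Simulation runs of the second row ranged from 0.6% to 0.7% certain and from 3.4% to 3.8% at 80% or more.

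Two things follow. Random lengths lose most of their benefit if they must add up to a total the guesser knows: the 48th place alone is then certain, which is 1/48 = 2.1%. And a length of 20 is not itself too short. The weakness is that it is fixed and disclosed.

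**The case against.** The strongest reply is that the route from foreknowledge to selection is narrow. Both women have consented and completed baseline before the envelope is opened. Envelopes carry participant IDs and are opened in ID order, which restricts swapping. Steering would have to act upstream and be timed to the last one or two places of a block. All of this stands, and it is why the point is modest.

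A second reply is that the article names one opener per centre and states that interviewers are masked. A reader might infer that site staff in general see every earlier assignment; the text does not support that. Facilitators learn who is in the intervention arm, and only the opener is shown to see the full sequence. Nor does the article say that the opener recruits. A condensed article may leave such role separation to the full protocol, so its absence is not the finding. The finding is the interval that the article does state.

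Third, the rule does not strictly exclude smaller blocks nested within 20. True, but the 20th assignment would still be known.

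Fourth, the effect is bounded. As an illustration with an assumed shift: if all 11 certain dyads were steered, half to each arm, with a 20-point shift in opposite directions, the bias would be 2 × (5.5 × 20/72), about 3 points. The design difference is 27 points (45% versus 72%). The illustration is extreme, and the result is still small beside the planned effect.

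**Conclusion.** The concern holds as a modest weakness in allocation concealment. The opener at each centre, and anyone told, can know the final assignment of every block. About 11 of 144 dyads (7.6%) are certain in advance, given equal sites, one permuted block of 20 between balance points, and an opener who keeps count. With unequal sites the figure changes slightly; the 9.1% per completed block does not.

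Two stronger readings are not supported. Nothing in the article shows that selection has occurred or will occur, so this is not evidence of bias. A reader might also infer that 48 per site, not being a multiple of 20, breaks the promised balance. The article promises balance at each interval of 20, not at the end of recruitment, and 48 per site is itself an assumption, so nothing is contradicted.

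**What to change.** Have the study statistician generate each site's list from permuted blocks of randomly varying, fairly large length, for example drawn freely from 12, 16, 20 and 24. Do not force the lengths to sum to a site target. Let the list run past the expected site total, so that the last dyads are not predictable from the total. Keep the lengths with the statistician only. In the Randomization section, replace the fixed interval with: *permuted blocks of randomly varying size, not disclosed to site staff*. If the opener is already kept away from recruitment, screening and scheduling, a short statement to that effect would help.

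The cost is one setting in the list software and one sentence. Envelopes, staff and sample size are unchanged. The price is that exact balance is no longer guaranteed at a fixed interval or at the end of recruitment. The change removes most near-certain assignments but does not lower the average guess rate. Short mixed blocks such as 4, 6 and 8 should be avoided, since they are more predictable on average than the present scheme.

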### Quantitative assessments and analytic plan

Quantitative data on feasibility (including recruitment, retention, adherence, and contamination) and safety of the intervention will be gathered through study records pertaining to recruitment, adherence, retention and safety. Data on empowerment of DILs and Mils (knowledge about safety and the links between DV and health, gender-equitable attitudes, decision-making skills, communication and social support, and resistance to DV) and incidence of DV and related health outcomes (e.g., quality of life, anxiety and depression, and maternal and infant health) will be gathered by research interviewers not involved in intervention implementation through face-to-face interviews. Interviews with DILs and MILs will be conducted individually at enrollment and 3 months and 6 months postpartum. Measures were chosen based on our theoretical approach and drawn from instruments used in our previous research, the Indian National Family Health Survey and studies of GBV and health in India and elsewhere (Table 3). Questions were selected keeping in mind the need to minimize study participation-related risks. For example, questions regarding MILs’ perpetration of violence will only be posed to DILs, and MILs’ experience of DV will also be posed in order to monitor safety of the intervention.

**Table 3 T3:** Measures

**Measure**	**DIL**	**MIL**

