**Feasibility and Safety**		
Recruitment, adherence, retention (proportion of eligible individuals who enroll, sociodemographic comparison of enrollees and non-enrollees, adherence to intervention and data collection visits, attrition)	X	X
Safety (e.g., number and nature of safety-related events)	X	X
Contamination (knowledge of neighbors, friends, or relatives participating in the intervention arm)	X^a^	X^a^

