**Outcomes**		
Domestic violence (measures of physical, sexual, and psychological acts of violence perpetrated by husbands, MILs, or other family members using an adapted Conflict Tactics Scale [54])	X	X
Perceived quality of life (WHOQOL-BREF [55])	X	X
Anxiety and depression (Kessler Psychological Distress Scale – K10)	X	X
Postnatal Depression (Edinburgh Postnatal Depression Scale [56])	X	
Maternal and Infant Health (maternal height, weight, weight gain during pregnancy, and BMI; infant weight, length, and head circumference)	X	

^a^Assessed only among control arm MILs and DILs.

Descriptive analyses will be conducted on data related to Aim 1 while data for Aims 2 and 3 will be analyzed using the intention to treat approach. Appropriate statistical techniques will be used to compare study arms on outcomes of interest (DILs’ and MILs’ empowerment, DV incidence, quality of life, anxiety and depression and maternal and infant health status) and, tailored by whether the outcome is binary, categorical, or continuous. Analytic models of intervention effect will include adjustments for individual-level demographic and background variables, such as age, education, and socioeconomic status, measured at baseline prior to randomization to examine for improved precision and to adjust for any (random) covariate imbalance across groups [57]. Longitudinal measurements of outcomes will be exploited using statistical techniques for matched or longitudinal analysis (matched pair analysis, before-after comparisons, generalized estimating equations for longitudinal models) to assess whether additional precision in efficacy estimates is possible. Finally, in the intervention group, we will explore the association between number of sessions attended by MILs and DILs and DV incidence to examine possible dose–response.

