### Qualitative assessments and analytic plan

We will gather in-depth information on study implementation-related issues that complement the quantitative data through three sets of 10 in-depth interviews (n=30) after the 6-month postpartum evaluation [58]. They include the following: (1) To better understand participants’ experience with and feedback on the intervention and its effectiveness, we will select, from the intervention arm, 5 DILs and 5 MILs who participated in all intervention sessions for an in-depth interview. These data will contribute to the refinement of the intervention curriculum to maximize its potential impact on DV. (2) To assess logistical, DV-related, or other barriers to intervention adherence and retention for improving a future phase 3 trial, we will interview 10 intervention arm participants who did not attend all scheduled sessions (that is, MILs who attended fewer than 5 sessions and DILs who attended only 1 or 2 out of 3 sessions, assuming they are not lost to follow-up). (3) To examine the presence of contamination, we will interview 10 DILs and MILs in representative proportions drawn from those control arm participants who reported knowing neighbors, friends, or relatives participating in the intervention arm at the 6-month postpartum interview. These interviews will focus on assessing extent of knowledge regarding the content of the intervention and ways in which this information may have influenced participants’ perspectives on gender equity and family relationships and perpetration and experience of DV.

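### A contamination item put only to control-arm women at the 6-month interview can reveal the arm to interviewers who are meant to be blind to it

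*Protocol article*

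**What the plan says.** The protocol article makes four statements that bear on this point.

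- **Randomization.** After randomization, session facilitators do not conduct follow-up interviews and the reverse, and "interviewers will not have access to information on treatment assignment".
- **Table 3, Feasibility and Safety rows.** One measure is "Contamination (knowledge of neighbors, friends, or relatives participating in the intervention arm"; it is marked for both daughters-in-law (DILs) and mothers-in-law (MILs). Footnote a to that row reads "Assessed only among control arm MILs and DILs".
- **Qualitative assessments and analytic plan.** The third set of in-depth interviews is drawn from "control arm participants who reported knowing neighbors, friends, or relatives participating in the intervention arm at the 6-month postpartum interview".
- **Quantitative assessments and analytic plan.** Empowerment, domestic violence (DV) and health data "will be gathered by research interviewers not involved in intervention implementation through face-to-face interviews". On timing, "Interviews with DILs and MILs will be conducted individually at enrollment and 3 months and 6 months postpartum". The same section opens by saying that "Quantitative data on feasibility (including recruitment, retention, adherence, and contamination) and safety of the intervention will be gathered through study records".

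**The concern.** An item asked in one arm only is a marker of that arm. Whoever administers it must know the assignment beforehand, or be told by a form or a skip instruction. If that person is also the outcome interviewer, the blinding promised under Randomization is lost at that visit.

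Participants cannot be blinded here. Table 1 has the envelope opened in front of the dyad, and the intervention consists of group sessions that the women attend. Keeping interviewers unaware of the arm is therefore one of the few safeguards available on the assessor's side. It matters most for answers given face to face about violence, attitudes, support, quality of life and distress, where probing and recording can be influenced by what the interviewer expects. The 6-month visit is the last assessment and closes the period used in the DV power calculation. The Discussion makes the effect on empowerment and the direction of trends in violence and health outcomes criteria for going on to phase 3.

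**Working it through.** No formula or stated figure is involved. The check sets the passages side by side.

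1. **What is promised.** Randomization: interviewers do not have assignment information. No visit is excepted.
2. **Who gets the item.** Table 3, footnote a: control-arm DILs and MILs only.
3. **What kind of item it is.** Whether a woman knows neighbors, friends or relatives in the intervention arm is something only she can report. It cannot come from attendance or enrollment logs alone.
4. **When it is answered.** Qualitative section: at the 6-month postpartum interview. No passage places it at enrollment or at 3 months.
5. **Who conducts that interview.** Quantitative section: research interviewers collect the self-reported outcomes at that visit. The article does not name who asks the contamination item. The study-records sentence points to a different source, and no sentence assigns the item to other staff or to a separate form.
6. **What follows if the outcome interviewer asks it.** Item present means control; item absent means intervention. Both arms are disclosed, although only one is asked.
7. **When the disclosure does harm.** The article does not give the order of questions.
   - If the item comes before the outcome modules, or the form itself differs by arm, the arm is known before the woman's answers are recorded.
   - If the item comes last on a form that otherwise looks the same, her own answers are already recorded. Dyads are randomized as pairs and interviewed individually, so the arm is still known before the second member's interview if the same interviewer sees both.

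**Extent.** There are two follow-up rounds (3 and 6 months) with two interviews per dyad in each, so 2 of 4 follow-up interviews per dyad fall at 6 months. With 144 dyads and the 90% retention assumed in the sample size section, 144 × 0.90 = 129.6, or about 130 dyads and 2 × 129.6 ≈ 259 interviews at 6 months. This is the most that could be touched. In the item-last case with a shared interviewer, at most one interview per dyad (about 130) would be exposed before its outcomes were recorded.

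**The case against.** The strongest reply is that the article never says the outcome interviewer asks the item. The quantitative section treats feasibility data, contamination included, as a stream separate from the interviewer-collected outcomes. A short item put by unblinded staff at the 6-month visit would satisfy every sentence. This stands in part. A reader might infer that the blinding rule and footnote a cannot both be followed. The text does not support that, because they conflict only if the outcome interviewer uses the item or an arm-specific form. It does not remove the problem: the answer is a self-report tied to that interview, and nothing in the article keeps it away from the interviewer.

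A second reply is that question order is operational detail which a condensed article may leave to the field manual. That is fair as regards order, and the absence of an order is not the point raised here. Footnote a is an explicit rule that one arm is asked and the other is not, and it has to be squared with an equally explicit blinding rule.

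A third is that other protections remain. That also stands. Facilitators and follow-up interviewers are kept apart, and many outcomes use structured instruments. A reader might infer that the whole of the Aim 2 and Aim 3 comparison is compromised. The documents do not support that either: the 3-month interviews are not shown to be affected, and maternal and infant measurements depend little on probing.

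Finally, women may let slip their arm anyway. Occasional disclosure differs from a disclosure built into the visit.

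**Conclusion.** The concern holds in conditional form. As written, a control-only contamination item reported at the 6-month interview can disclose the arm to an interviewer who is supposed not to know it. The passages on blinding, on the source of contamination data and on the 6-month report need to be reconciled.

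The exposure is confined to interviewer-recorded self-reports at 6 months, at most about 259 interviews under the plan's own retention assumption. It rests on the assumption that the outcome interviewer asks the item or sees an arm-specific form; for the second dyad member in the item-last case, it also rests on one interviewer seeing both women. Neither the direction nor the size of any resulting bias can be obtained from the document, so none is claimed. The case for acting is that the final self-reported outcomes feed the phase 3 decision and that the remedy costs almost nothing.

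**What to change.** - Use one identical 6-month form for DILs and MILs in both arms, with no arm-specific version or skip.
- Put a neutrally worded contamination item after all outcome modules, for example whether the woman knows anyone who attends the group sessions.
- Ask it only once the outcome interviews of both dyad members are complete, or have existing non-interviewer staff ask it at that point. The timing is essential: an intervention-arm woman may answer that she attends the sessions herself, so neutral wording alone does not keep the arm hidden.
- Use only the control-arm answers for the contamination estimate and for choosing the in-depth interviewees, so that Aim 1 loses nothing.
- Amend Table 3 footnote a to say that both arms are asked and only control answers are analyzed. Amend the study-records sentence and the qualitative section to state who asks the item and when.

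The cost is one or two extra questions for intervention-arm women and a change to the form. No added visit or staff is needed. Where the two members of a dyad are interviewed on different days, the item has to wait for the second interview.
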